### Intervention

#### Design of the mHealth App

For the design of the mHealth app, the expert consensus and the modified Delphi will be used. The consensus conference will consist of 12 experts, with 2 representatives having each of the following profiles: (1) health care professional with experience (>5 years) in the care of patients with multimorbidity or HF; (2) university teaching and research staff with experience in research projects in the thematic areas addressed (HL; intervention programs, or patients with multimorbidity); (3) other professionals with experience in research, assistance, or care of patients with multimorbidity (social workers, psychologists, communication professionals); (4) computer engineers with experience in the design of information and communication technology tools; (5) representatives of associations of patients with chronic diseases; and (6) patients with multimorbidity and HF. The consensus sessions will incorporate the main agreements adopted regarding the contents of the intervention program, format, logistical coordination for the development of the program, and proposals for sustainability. Once consensus has been reached, the contents will be established together with the graphic script of the future tool. Delphi rounds will validate the content of the wireframes and the storyboard in terms of relevance (significance of the content for the objective of the intervention program) and appropriateness (content fit). The optimal size for a Delphi group is estimated to be between 6 (minimum) and 30 (maximum) [37]. Considering the response/abandonment rate, we will try to tend to the maximum number of experts who will be different from those that participated in the consensus conference but will meet the same criteria. A 4-point Likert scale (1=no relevance/adequacy and 4=high relevance/adequacy) will be included with each content screen. The experts will be required to evaluate the content’s relevance and appropriateness in each screen. The Content Validity Index (CVI) [38] of each screen will be calculated.

Similarly, the Adequacy Index (AI) will be analyzed. The relevance/appropriateness of the screens will be considered good if the CVI and AI are greater than or equal to 0.78 [38]. Those screens that do not reach the preset value in the aforesaid indices will be reviewed and reformulated. Screens’ content will also be modified based on the feedback collected and subjected to the same process described above until a final version is agreed upon. This prototype will be sent to a developer to create the mHealth tool under an agile approach. This process (designing, creating, and developing the mobile app) will take 18 months.

#### Description of the Intervention

The mHealth app aimed at empowering HL and self-management of the patients with multimorbidity with HF and complex health needs. It will be developed ad hoc based on the information obtained from the consensus sessions of experts (patients and professionals) and in accordance with the gamification methodology [39]. Although the final choice of the content will depend on the resulting decisions of the experts, it is intended to offer information and resources to the patient according to the level of HL identified and considering the main actions recommended to be incorporated to improve the overall health outcomes of these patients [12]. Thus, the participants in the experimental group will receive the mHealth app and will agree with the health care professional on 3 objectives related to the self-management of their disease, which they will have to achieve within a proposed period, being assisted by the mobile app, which will provide feedback and reinforcement in the achievement of these objectives. The stages and timing are described in Table 1. The intervention carried out in the control group participants will be based on usual clinical practice. Like the experimental group, they will agree with the health professional on 3 objectives they will have to achieve within the proposed time frame. This process (evaluation of the efficacy of the mHealth intervention with 2 groups) will last 12 months.

**Table 1 table1:** Stages of intervention.

Stage	Description	Timing (months)												
0	Detection of potential study participants. Presentation of the project and collection of informed consent.	✓^a^												
1	Baseline data collection for both groups.	✓												
2	For both groups, the patient and the practitioner will agree on the first health goal. On an individual basis, the nurse will present the main aspects related to the use and management of the app to the members of the expert group. The patient’s expectation of self-efficacy in using the app will be assessed to prevent adherence problems concerning the use of mobile health and difficulties in using the app (digital literacy) will be resolved.	✓	✓	✓										
3	The patient will come for a consultation to check compliance with the chosen objective. If necessary, a simulation test will be performed to confirm that the challenge has been met. At the end of this stage, the patient and the multidisciplinary team will agree on the second objective.			✓	✓	✓	✓							
4	Check compliance with the second objective. Perform simulation test, if required. At the end of this stage, the patient and the multidisciplinary team will agree on the third objective.						✓	✓	✓	✓				
5	Check compliance with the third objective. Perform simulation test, if required.									✓				
6	Postintervention evaluation: all health objectives were achieved by the patient and postintervention evaluation is performed										✓	✓	✓	
7	Follow-up	At 12 months after the intervention												

^a^✓: achievement record.

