#### Completion Criteria and Withdrawal

A patient will be considered to have completed the study when he/she completes the postintervention evaluation. The criteria for withdrawal of a participant will be

failure to receive the complete intervention (unsolvable technical failures in the device) or by the protocol (failure to use the app);loss of compliance with the eligibility criteria during the study or withdrawal of consent to participate;inability to contact for follow-up.

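### Table 1 ties the only post-intervention evaluation to having achieved every health objective and gives non-achievers no route to it; the 12-month anchors also need reconciling

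*Protocol article*

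**What the plan says.** Under Description of the Intervention, patients in both arms agree three self-management objectives with a professional. In the app arm they pursue them "being assisted by the mobile app, which will provide feedback and reinforcement in the achievement of these objectives". In the control arm, under usual practice, "they will agree with the health professional on 3 objectives they will have to achieve within the proposed time frame".

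Table 1 then sets out the stages. Stages 3 to 5 check compliance with each objective in turn, with a simulation test where needed. Stage 3 closes with "At the end of this stage, the patient and the multidisciplinary team will agree on the second objective", and Stage 4 does the same for the third objective. Stage 6 is "Postintervention evaluation: all health objectives were achieved by the patient and postintervention evaluation is performed", marked in three adjacent monthly columns. Stage 7 is follow-up, timed "At 12 months after the intervention".

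Under Completion Criteria and Withdrawal: "A patient will be considered to have completed the study when he/she completes the postintervention evaluation". The withdrawal criteria that follow begin with "failure to receive the complete intervention (unsolvable technical failures in the device) or by the protocol (failure to use the app"), then loss of eligibility or consent, then loss of contact. Failure to achieve an objective is not among them.

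On duration, the text before Table 1 says: "This process (evaluation of the efficacy of the mHealth intervention with 2 groups) will last 12 months". Table 3 lists readmissions at 1 and 12 months without saying from when they are counted.

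**The concern.** Stage 6 is the only post-intervention evaluation in the schedule, and its description includes success on every objective. A site that follows the table as written has no instruction to evaluate a patient who missed one.

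Achievement happens after randomisation, and the app is designed to raise it. If only achievers are measured, the comparison is between two subsets selected under different conditions, and randomisation no longer protects it. The affected outcome is health literacy on the HLS-EU-Q47, which the Sample Size section names as the main outcome. An outcome never collected from non-achievers cannot be recovered by later analysis, so this has to be settled in the protocol and before evaluations start.

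The second issue is smaller and separate. A follow-up dated from the end of the intervention falls after the patient has, by definition, completed the study. A reader cannot tell whether the 12-month readmission count belongs to the 12-month evaluation process or to Stage 7.

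**Working it through.** **Reading the text.** Four places bear on who is evaluated:

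1. Stage 6 joins achievement of all objectives and the evaluation in a single description.
2. Stages 3 to 5 check compliance, and the next objective is agreed at the end of the stage. They do not state success as a condition for moving on.
3. The completion rule refers to the evaluation and does not mention objectives.
4. The withdrawal list does not include failing an objective.

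Item 1 points towards evaluating achievers only; items 2 to 4 do not support that restriction. No sentence resolves the matter by saying that all randomised patients are evaluated.

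**What a literal reading could do to the result.** The article gives no achievement rates, no correlation between achievement and health literacy, and no bias figure, so there is no stated figure to reproduce. What follows is an illustration.

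Inputs from the Sample Size section: mean 32.88, SD 6.10, and a relevant increase of 10%, which is 0.10 × 32.88 = 3.288 points.

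Assumptions: the app has no true effect on health literacy; achievement is the upper part *p* of a latent normal score that correlates *r* with the HLS-EU-Q47 score; *r* and the SD are the same in both arms; only achievers are evaluated.

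The mean of the evaluated group is then raised by *r* × SD × λ(*p*), where λ(*p*) = φ(z)/*p* and z is the cut-off for the top fraction *p*.

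- Top 50%: λ = 0.798
- Top 70%: λ = 0.497
- App minus control, at 70% and 50%: *r* × 6.10 × (0.497 − 0.798) = *r* × (−1.84)
- *r* = 0.2: −0.37 points, 11% of 3.288
- *r* = 0.3: −0.55 points, 17%
- *r* = 0.5: −0.92 points, 28%

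Other assumed rates:

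| Control / app achieving all | Shift at r = 0.2 | Shift at r = 0.5 |
|---|---|---|
| 50% / 70% | −0.37 | −0.92 |
| 60% / 80% | −0.36 | −0.90 |
| 70% / 80% | −0.18 | −0.45 |
| 50% / 50% | 0 | 0 |
| 80% / 60% | +0.36 | +0.90 |

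The arm with fewer achievers is the more strongly selected, so its mean is raised more. The shift therefore runs against the arm with more achievers.

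**Timing.** Three statements stand side by side: the efficacy evaluation lasts 12 months; the patient completes the study at Stage 6; Stage 7 comes 12 months after the intervention. A 12-month readmission count could start at baseline and fit the first statement, or start at the end of the intervention and fit the third. In the second case it would be collected after the patient has completed the study.

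**The case against.** The strongest reply is that Stage 6 describes the expected state of a patient at the end of the pathway and sets no condition. It uses no conditional word, the earlier stages do not require success, and failing an objective is not a reason for withdrawal. All of this stands. A reader might infer that the protocol excludes non-achievers from evaluation; the article does not say so. What remains is that the only wording on the evaluation assumes success, and nothing tells a site what to do otherwise.

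A reader might also infer that each patient's evaluation date depends on how fast objectives are reached. The article does not support that. Stage 6 is a calendar window of three monthly columns, and nothing makes the date of achievement the trigger. A tighter visit window is also the sort of detail an article can leave to the full protocol.

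It can further be said that the rates and the correlation are assumed, that the modelled shift vanishes when rates are equal, and that with more achievers on the app it would work against the app and so would not create a false benefit. This is correct, and it is why the figures serve only as illustration. A bias against a working app is still a bias in the primary comparison.

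On timing, Stage 7 may simply be a later follow-up, with completion marking the end of the intervention phase. That is a possible reading, but it still does not say when the 12-month readmission count starts.

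**Conclusion.** The point holds as a defect of wording with a potentially serious consequence. The selection is implied by Stage 6 and stated nowhere. If sites follow the table literally and achievement rates differ between arms, the health literacy comparison is made between subsets chosen after randomisation. Neither the size nor the direction of the bias can be derived from the article. Under the assumed 50% against 70% achievement and correlations of 0.2 to 0.5, the shift is about 0.4 to 0.9 points, or 11% to 28% of the 3.288-point target. If non-achievers are in fact evaluated, this problem does not arise.

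The timing point rests on the text alone: Stage 7, the completion rule and the 12-month duration do not together identify when the 12-month readmission count begins.

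**What to change.** - Reword Stage 6 so that every randomised patient has the post-intervention evaluation in the same scheduled window counted from randomisation, whether or not objectives were achieved.
- Record the number of objectives achieved as a process variable.
- Name that evaluation as the primary time point for health literacy.
- Reconcile Stage 7, the completion rule and the 12-month readmission count with the 12 months given under Description of the Intervention, and state the date from which readmissions are counted.

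The cost is a change of wording and some additional evaluations in patients who did not achieve their objectives. Their number depends on achievement rates that the article does not give. Under the 50% and 70% illustration with 118 per arm it would be 118 × 0.5 = 59 control patients and 118 × 0.3 ≈ 35 app patients, before any loss to follow-up.

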### Process

#### Assessment Eligibility

The health care professionals participating in the study will verify that the patient meets the eligibility criteria by consulting the digital history and interviewing the patient.

#### Randomization

Block randomization has been considered. The total number of participants will be divided by the number of study centers in equal parts. The number assigned will be for each center and will be considered a block in terms of randomization. An external collaborator (blinded) will use a computer-generated randomization list to assign patients to the groups such that, in each block (center), 50% of the patients will go to the control group (usual clinical practice) and 50% to the intervention group (usual clinical practice and mHealth app). This information will be available only to the principal investigator.

#### Masking

Because of the characteristics of the study, it is not possible to blind it to the participants or to the researchers who will carry out the intervention. However, it will be masked to the researchers who will perform the effectiveness evaluation and data analysis. For this purpose, the coding of the randomization variable will be hidden from them and will be guarded by a person outside the project selected by the principal investigator. In this way, it will not be possible to know which groups received the intervention until the analyses are completed.

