**Secondary response**				
	Personal autonomy basic activities of daily living	0-100	Barthel Index [35]	Registration
	Personal autonomy instrumental activities of daily living	0-8	Lawton-Brody Index [42]	Registration
	Therapeutic adherence	0-4	Morisky-Green Adaptation Questionnaire [43] and Recipe XXI	Registration
	Vital forecast	0-30	PROFUND Index [44]	Registration
	Satisfaction with service	0-10	Satisfaction Scale	Nursing record
	Mobile health device satisfaction	1-5	Satisfaction Scale	Built-in mobile health device registration

^a^HLS-EU-Q47: 47-item European Health Literacy Questionnaire.

^b^NOC: Nursing Outcomes Classification.

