### Data Analysis: Data Encoding

A data matrix will be created, and data will be processed statistically using SPSS, version 22 (IBM). Statistical significance will be set at 95% (α=.05).

A uni-bivariate descriptive analysis will be performed to determine the sample distribution for each of the variables studied, both for the total sample and for each group. The characterization variables will be summarized using descriptive statistics, expressing qualitative variables in terms of frequency and percentages and quantitative variables in terms of mean and SD.

Before the analysis, the normality of the variables will be evaluated using the Kolmogorov-Smirnov and Shapiro-Wilk tests. Baseline differences in the variables related to the sample profile between the intervention and control groups will be compared using the Student *t* test when these are normally distributed and the nonparametric Mann-Whitney *U* test in case they are not. Differences between dichotomous qualitative variables will be established using the chi-square test or Fisher statistic when appropriate.

A contrast of means will be applied to test the efficacy of the intervention in terms of the normality distribution of the variables. The results will be analyzed using the nonparametric Wilcoxon signed-rank test, which will allow us to check if there are differences between 2 populations from 2 dependent or related samples, or the Student *t* test for normally distributed samples. For independent samples, the nonparametric Mann-Whitney *U* test will be used.

The strength of the relationship between continuous data will be determined from the Pearson or Spearman correlation. The intraclass correlation coefficient will be used if it is necessary to measure concordance between measurements at different times of the study. To identify sociodemographic and clinical characterization variables (independent variables) related to the intervention and the different response variables (dependent variables), multivariate, linear, logistic, or Cox proportional analyses will be performed, as appropriate for each response variable.

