### Limitations

This study has some limitations that should be acknowledged. The lack of adequate mobile devices or the sensory or cognitive deficits of the target population is taken into account. Likewise, their digital illiteracy could be another limitation. Therefore, and being aware of the population group, digital training is contemplated. As for cognitive impairment, the usual caregiver is included in the intervention.

When evaluating the effectiveness of the intervention, we can find the influence of the variable “time of use of the app” (a record of access to the app will be obtained and monitored).

Finally, we must be aware of the possible loss of participants due to their clinical characteristics. Therefore, when determining the sample size, a loss rate of 30% has been taken into account. The aim is to obtain as many participants as possible to increase the precision of the estimates.

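### Hiding the arm code does not keep the analysts masked as claimed, because one listed secondary response is recorded only inside the app

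*Protocol article*

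**What the plan says.** The Masking section accepts that participants and the staff delivering the intervention cannot be blinded. For the rest of the team it says "it will be masked to the researchers who will perform the effectiveness evaluation and data analysis". The means is that "the coding of the randomization variable will be hidden from them and will be guarded by a person outside the project", and the result is stated without qualification: "In this way, it will not be possible to know which groups received the intervention until the analyses are completed".

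Four other places bear on this:

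- **Description of the Intervention:** the experimental group receives the app, and the control group has usual clinical practice.
- **Table 3, secondary responses:** "Mobile health device satisfaction", scored 1 to 5, has as its data source "Built-in mobile health device registration". Satisfaction with the service is a separate row, scored 0 to 10.
- **Data Analysis:** one data matrix is created, and the descriptive analysis is to give the "sample distribution for each of the variables studied, both for the total sample and for each group".
- **Limitations:** because time of app use may influence the evaluation of effectiveness, "a record of access to the app will be obtained and monitored".

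**The concern.** Hiding the meaning of a group code masks an analyst only if nothing else in the file distinguishes the arms. A variable that can exist in one arm alone does distinguish them: whichever coded group has values is the app group. The article lists such a variable among its responses and asks for each variable to be described by group, so its promise of masking until the analyses are complete conflicts with its own variable list.

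This matters because masking of evaluators and analysts is the only masking the trial has, and the abstract calls the trial blinded. Analyst masking protects decisions made after the data are seen. The Data Analysis section leaves some of these open, notably which multivariable model and which characterization variables to use for each response. The point concerns the analysts and their data file, not who records data at the sites.

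**Working it through.** The article states no figure for this point, so there is none to reproduce. The check traces the variables through the plan.

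**1. What the mask consists of.** Only the coding of the randomization variable is hidden. The analysts still work with two separable coded groups, as a description by group requires.

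**2. Which variables can exist in one arm only.**

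- *App satisfaction:* a listed secondary response whose source is the app. A control patient has no app and so cannot have a value. Since satisfaction with the service has its own row, this row cannot be read as a general measure for both arms. This is firm evidence.
- *App-access record:* mentioned under Limitations but in neither Table 2 nor Table 3. It would reveal the code in the same way if placed in the analysts' file, which the text does not state.
- *Expected self-efficacy with the app:* Table 1, stage 2, says "The patient’s expectation of self-efficacy in using the app will be assessed", but the item is not in the variable tables. The same condition applies.
- *Withdrawal for not using the app:* given as a withdrawal criterion, not as an analysed variable. The same condition applies.

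The finding rests on the first item alone.

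**3. Whether that item is tabulated by group.** It is a listed response, so it falls within the variables to be described in total and by group. No passage withholds it or holds it in a separate file.

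**4. Whether timing rescues the claim.** The Data Analysis section presents description first, then normality checks, then the efficacy contrast, but this is paragraph order and not a stated rule. The claim does not need it. Masking is promised until the analyses are completed, and app satisfaction is one of the responses to be analysed. Examining it by coded group at any time before that end point opens the code.

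**5. How many completed items are needed.** One is enough. Let n be the number of app-arm patients and c the completion rate, with independent completion assumed. The chance of at least one value is 1 − (1 − c)^n. The article gives no c, so a range is shown. It plans 118 per group and allows for 30% loss; 118 × 0.7 = 82.6, taken as 82.

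| Assumed c | n = 118 | n = 82 |
|---|---|---|
| 1% | 1 − 0.99^118 = 0.69 | 1 − 0.99^82 = 0.56 |
| 5% | 1 − 0.95^118 = 0.998 | 1 − 0.95^82 = 0.985 |
| 20% | about 1.00 | about 1.00 |

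These figures assume that the item is in the file the analysts use with the coded arm. They show that incomplete data would not protect the mask; they do not prove that the item is in that file.

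**The case against.** The strongest reply is that a journal article need not describe data exports. The contents of the data matrix are not listed, app satisfaction has its own data source, and the full protocol or a data management plan could link it only after the code is opened. If so, the mask would hold. The reply is fair as to what may happen in practice, and it means that unmasking is conditional on the item being in the coded file. It does not remove the contradiction. The article names the mechanism, the hidden coding, and derives the guarantee from it. With this variable list and description by group, that mechanism cannot deliver the guarantee.

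Three further objections stand:

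- The access record and the app-related withdrawal reason are not shown to enter the data matrix.
- A reader might infer that the code is certain to be broken before efficacy is tested. The documents do not support this: it needs both an explicit order of work and confirmation of the file's contents, and the article gives neither.
- A reader might also infer that the main comparison is left to an unmasked analyst's discretion. The text does not say so. The choice between parametric and nonparametric tests follows normality results, and the models selected to suit each response serve to identify related characterization variables, separately from the contrast of means that tests efficacy.

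**Conclusion.** The concern holds in limited form. The statement that the groups cannot be known until the analyses are completed is not true of the plan as written, because one listed secondary response exists only in the experimental arm and is to be described by coded group. This rests on the app-satisfaction item alone. It assumes that the item sits in the analysts' file as the Data Analysis section implies, and that at least one patient completes it.

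The size of any resulting bias cannot be derived from the article. It is probably modest, since the choice of efficacy test is tied to normality results and the exposed latitude lies mainly in the multivariable models. The flaw does not invalidate the trial, but it should be corrected because the fix is cheap and this is the only masking available.

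**What to change.** Amend the Masking and Data Analysis sections to state that:

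1. until the between-arm analyses are locked, the analysts' file holds only variables collected in both arms, under neutral arm labels;
2. app satisfaction and any other app-generated data, including the access record, stay with the outside custodian who already holds the code;
3. these data are released once the between-arm analyses of the main and secondary responses are locked, and are then reported as description of the experimental arm.

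The by-group description should be limited accordingly to variables collected in both arms while the mask is in force.

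The cost is a few sentences, a second data export and slightly later app-use analyses. No extra patients, visits or staff are needed.
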